## Abstract

**Background:**

Hypertensive disease in pregnancy remains the leading cause of maternal mortality in the Netherlands. Seventeen percent of the clinical pregnancies are complicated by hypertension and 2% by preeclampsia. The Dutch Society of Obstetrics and Gynaecology (NVOG) has developed evidence-based guidelines on the management of hypertension in pregnancy and chronic hypertension. Previous studies showed a low adherence rate to other NVOG guidelines and a large variation in usual care in the different hospitals. An explanation is that the NVOG has no general strategy of practical implementation and evaluation of its guidelines. The development of an effective and cost effective implementation strategy to improve adherence to the guidelines on hypertension in pregnancy is needed.

**Methods/Design:**

The objective of this study is to assess the cost effectiveness of an innovative implementation strategy of the NVOG guidelines on hypertension including a computerised decision support system (BOS) compared to a common strategy of professional audit and feedback. A cluster randomised controlled trial with an economic evaluation alongside will be performed. Both pregnant women who develop severe hypertension or pre-eclampsia and professionals involved in the care for these women will participate. The main outcome measures are a combined rate of major maternal complications and process indicators extracted from the guidelines. A total of 472 patients will be included in both groups. For analysis, descriptive as well as regression techniques will be used. A cost effectiveness and cost utility analysis will be performed according to the intention-to-treat principle and from a societal perspective. Cost effectiveness ratios will be calculated using bootstrapping techniques.

## Background

Hypertension is a common complication of pregnancy. Seventeen percent of the clinical pregnancies are complicated by hypertension and 2% by preeclampsia [1-6]. Severe hypertension and preeclampsia (hypertension and proteinuria) pose an increased risk for morbidity and mortality to both the mother and the foetus. Major maternal complications (*e.g*., eclampsia, HELLP syndrome, pulmonary oedema, placental abruption, liver haematoma, severe infectious or thrombotic morbidity, encephalopathy) were recently reported in 74 of 216 (34%) Dutch pregnant women with severe hypertension or preeclampsia [7,8]. The Dutch trends in maternal morbidity due to severe hypertension and preeclampsia are currently a reason for great concern [9]. Hypertensive disease in pregnancy remains the leading cause of maternal mortality in the Netherlands, followed by thromboembolism and obstetric haemorrhage. Fifty-one percent of the total number of maternal deaths is a result of hypertensive complications in pregnancy. The maternal mortality ratio (MMR; deaths per 100,000 live births) from hypertensive disease in pregnancy increased from 2.7 in 1983 to 1992 to 4.0 in 1993 to 2002 [10], a major difference with surrounding countries. In the UK, maternal mortality due to hypertensive disease ranks fourth place-- with a MMR of 0.7 -- following thromboembolism, obstetric haemorrhage, and death during first trimester (ectopic pregnancies, miscarriage, and termination of pregnancy) [11].

It is thought that a high degree of these maternal complications results from suboptimal or insufficient treatment [12,13]. A recent study of the Dutch Committee on Maternal Death showed that in 96% of the cases of maternal death due to hypertensive disease several factors of substandard care were present. For instance, in 85% of this patient group, treatment of severe hypertension was inadequate. In many cases, the decision to start therapy was either made too late or not at all [14]. Therefore, management of hypertension is an important part of care for pregnant women for which improvement is necessary. To support their members, the Dutch Society of Obstetrics and Gynaecology (NVOG) has developed evidence-based clinical guidelines on the management of hypertension in pregnancy [15] and chronic hypertension in pregnancy [16]. However, these guidelines are not yet implemented. The NVOG has no general strategy of practical implementation and evaluation of its guidelines, and has only just begun with a policy of hospital visitations in order to improve quality of clinical care. In order to reduce maternal complications, an implementation strategy to improve adherence to the guidelines on hypertension in pregnancy is necessary

Original studies and systematic reviews about the effectiveness of different interventions to change clinical practice show that a widely used strategy for implementing guidelines consists of audit and feedback about actual performance. This strategy has shown to be effective, but feedback is often recommended in combination with other strategies [17]. In a recent systematic review, a major benefit of implementing health information technology on increased adherence to guideline-based care was demonstrated, including hypertension [18]. Different health information technology systems were reviewed. Most of them included a decision support system, and some of them integrated clinical guidelines [19]. In case of hypertension in pregnancy, an implementation strategy including a computerised decision support system (BOS) may lead to a higher compliance to the guidelines' recommendations and thus a lower rate of maternal complications and their costs. This will be tested in this study.

It is expected that an increased adherence to the guidelines' recommendations will reduce the number of major maternal complications. By reducing the number of major maternal complications, we expect a reduction in health care costs (*e.g*., costs of hospitalisation, medication), costs in other sectors, patient and family costs, and costs of production losses [20]. Estimating the size of this cost reduction is an essential part of this study.

## Objectives

The objective of this study is to assess the effectiveness and cost effectiveness of an innovative implementation strategy of the NVOG guidelines on hypertension, including a computerised decision support system compared to a common strategy of professional audit and feedback.

The research questions are:

1. To what extent is an innovative strategy using a computerised decision support system cost effective compared to a common strategy of professional audit and feedback in implementing the NVOG guidelines on hypertension in pregnancy?

2. What is the feasibility of the two implementation strategies?

3. What is the cost effectiveness of the two strategies to implement the guidelines on hypertension in pregnancy in clinical practice?

## Methods/Design

### Study design

A cluster randomised controlled trial with an economic evaluation alongside will be performed. The chosen implementation strategies are:

1. A common strategy consisting of professional audit and feedback.

2. An innovative strategy including a BOS tailored to the barriers and facilitators that are found in a pilot study and professional audit and feedback.

### Preparation

The first part of the study consists of the development of a set of quality indicators extracted from the NVOG guidelines on hypertension in pregnancy. The indicator development will be performed according to the RAND-modified Delphi method [21]. First, key recommendations from the guidelines will be extracted by two or three experts (project leaders). Subsequently, the relevance of all key recommendations for patient's health benefit (clinical relevance) and efficacy will be tested in two rounds among an independent panel of 12 to 15 experts. The opinion leaders of clinical obstetrics, in particular regarding hypertension in pregnancy, as well as members of the NVOG committees on maternal death, guidelines, implementation and quality, quality of care experts, and patients' organisation Stichting HELLP are involved in this expert panel. The key recommendations with the highest scores will be selected and operationalised in measurable elements (process indicators). Based on this set of quality indicators, the BOS for the guidelines on hypertension in pregnancy will be further developed. Moreover, measurement instruments will be developed and the participating hospitals will be informed about the study.

Ethical approval was granted june 12^th ^2008, reference number 2008/138.

### Pilot study

The innovative strategy will be tested in one of the participating hospitals to explore its feasibility.

### Implementation study

An effect and process evaluation will be performed. An effect evaluation of the two strategies will be carried out using the primary and secondary outcome measures. This will be done among pregnant women who develop severe hypertension or preeclampsia and professionals involved in the care for these women. The measurements will be performed in 20 participating hospitals before and after implementation of the different strategies by a medical record search, added with questionnaires among professionals and patients. The medical record search will be done using standardised registration forms. Follow-up of the patients will be six months after delivery.

A process evaluation will be performed to study the feasibility of the two strategies. The extent by which clinicians, nurses, and patients used BOS and the other elements of the strategies (audit and feedback) and their experiences with these elements will be measured. The process information regarding to what extent professionals used BOS will be collected by the application itself. The system will register relevant data of participating professionals and their patients. This will allow us to analyse the relation between the use of BOS and the primary and secondary outcome measures. To measure the experiences with BOS and the other elements of the two strategies, personal interviews will be held among 10 to 15 gynaecologists, nurses, and patients. This will provide insights into possible barriers and facilitators for and satisfaction with using BOS. The possible barriers and facilitators will be quantified with questionnaires among all participating professionals and patients.

For analysis, descriptive as well as regression techniques will be used. A cost effectiveness and cost utility analyses will be performed according to the intention-to-treat principle and from a societal perspective. Cost effectiveness ratios will be calculated using bootstrapping techniques (see economic evaluation).

### Participants

Gynaecologists of 20 Dutch hospitals (university-based, teaching and non teaching) will be invited for participation. Pregnant women who develop severe hypertension or preeclampsia (in accordance to guidelines definitions) in these hospitals will be included. It appears from Dutch data that immigrants are at increased risk for preeclampsia [22]. This is the reason why patient characteristics like age, race, and cultural background will be included in a multilevel analysis. Exclusion criteria are refusal to participate or a diagnosis of lethal fetal congenital abnormalities.

This study will be conducted within the framework of the Otterlo group (a NVOG working group that develops obstetrical guidelines). Representatives of eight academic hospitals and two large teaching hospitals participate in this group. Representatives of another 10 related hospitals will be invited to participate. These hospitals are currently collaborating in the Dutch Perinatal Research Consortium http://www.studies-obsgyn.nl/index.asp.

### Interventions

Innovative strategy including a computerised decision support system. We performed a pilot-study to make an inventory of the barriers and facilitators for adherence to the guidelines on hypertension in pregnancy. Barriers can arise at different stages in the healthcare system at the level of the individual professional (*i.e*., lack of knowledge or skills, resistance against working with protocols); of the healthcare team (*i.e*., lack of knowledge or skills, insufficient collaboration); of the patient (*i.e*., unwillingness, difficult guideline adherence for some patient groupes); of the healthcare organisation (*i.e*., lack of registration/information systems, time restriction for adequate care); and of the wider environment (*i.e*., lack of financial incentives, misuse of guideline in medical disciplinary law) [20]. Barriers can also arise at the level of the innovation (guideline) itself (*i.e*., doubting evidence of the guideline, poor layout, unclear decision tree, unclear content). In a pre-study among 14 gynaecologists in 11 different hospitals (university medical centres, teaching and non-teaching hospitals), we determined which barriers at which level were present regarding the implementation of the guidelines on hypertension in pregnancy. The main barriers proved to be at the level of the guideline itself. A poor layout to use the guideline showed the highest score (64%). Doubt about a clear decision tree behind the guideline scored also high (57%). Furthermore, 36% of the gynaecologists mentioned that 'the guideline could easy be misused in medical disciplinary law,' 'the content of the guideline was unclear,' and that 'there was not enough room to consider patients wishes.' Moreover, 50% of the gynaecologists doubted about the accuracy of certain parts of the guideline. The implementation strategy will be based on these barriers and facilitators. We will use a computerised decision support system, which is a commercial web application developed by Giant-Soft in Leeuwarden, the Netherlands. A similar system has been tested and evaluated using another clinical guideline. The system appeared feasible in clinical practice: most users (95%; 34 of 36) were satisfied with its use and 78% (28 of 36) would prefer to maintain and extend the application to other guidelines [23,24]. In our opinion, BOS can be a solution for the main barriers regarding layout of, and decision tree behind, the guideline. In this way, BOS is tailored to the barriers 'possible misuse in the medical disciplinary law' and 'not enough room to consider patients' wishes.' In this strategy, we will combine BOS with professional audit and feedback (see control intervention).

### Control intervention

The control intervention will consist of professional audit and feedback only. We will perform a retrospective medical record search (audit) for patients with preeclampsia in the 20 hospitals, university hospitals, teaching and non-teaching hospitals. These records will be checked for the extent of adherence to the quality indicators developed from the guideline *Hypertensive Disorders In Pregnancy*. Feedback about the results of the audits will be given in a face-to-face meeting.

## Outcome measures

### Primary outcome

The primary outcome measure for the evaluation of the effectiveness of both strategies is a combined rate of major maternal complications (maternal death, organ specific complications of hypertension, HELLP syndrome, placental abruption).

### Secondary outcomes

Secondary outcome measures for effectiveness are guidelines' adherence rates, fetal death rates, Caesarean delivery rates, and rates of neonatal mortality and morbidity. To measure guidelines' adherence rates, process indicators will be established after selection of key recommendations with the highest scores in the RAND-modified Delphi method.

In the process evaluation, experiences with the implementation strategies are measured. This includes both parameters regarding the participation and presence of the professionals at the feedback meeting and patients in the implementation activities; in particular, the use of the BOS application at patient level as parameters regarding their satisfaction with BOS and the other implementation activities and their meaning about the feasibility (barriers and facilitators) of these activities.

### Sample size

The rate of major maternal complications in 216 Dutch patients with severe hypertension or preeclampsia was reported as 34% [7,8]. In 96% of cases of maternal death, care was suboptimal with insufficient treatment of hypertension in about half of these [14]. It is expected that an increased adherence to the guidelines' recommendations will reduce the number of major maternal complications by one-half, *i.e*., from 34% to 17%. Considering an intracluster correlation of 0.05, 20 hospitals will have to be included with approximately 20 patients each in order to get a reliable estimate (alpha = 0.05; power = 0.80) of a 50%-difference (34 verus 17%) in major maternal complications between both groups. If it is assumed that 15% of participants will drop out or be lost to follow up, 472 eligible women will have to be included. It also is assumed that the total number of deliveries in the participating hospitals is 30,000 (during 18 months of inclusion in 20 hospitals) and the incidence of severe hypertension and preeclampsia is 2%. It is estimated that the source

population consists of 600 eligible women. Thus, the expected number of inclusions per month will be 33 in 20 hospitals, *i.e*., one or two per hospital. The minimum required number of inclusions for randomisation per month is 26 [see figure 1 for flowchart].

**Figure 1 F1:**
[figure not shown]
**flowchart randomisation and inclusion**.

### Data analysis

To analyse the effectiveness of the two implementation strategies with regard to the primary and secondary outcomes and process indicators, descriptive as well as regression techniques will be used. The analysis will include an elementary head-to-head comparison of the two intervention groups, as well as a multi-level analysis. The latter will incorporate the levels of gynaecologist, patient, and time measurements. The process information regarding to what extent professionals used BOS will allow us to analyse the relation between the use of BOS and the primary and secondary outcome measures. Process information will also give us insight into the experiences of the participants (both satisfaction and feasibility) with the BOS and the other implementation activities.

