### Economic evaluation

The economic evaluation (cost effectiveness and cost utility analysis) will be performed according to the intention-to-treat principle and from a societal perspective. Healthcare costs (costs of hospitalisation, medication), costs in other sectors, patient and family costs, and costs of production losses are included. Quality adjusted life years (QALYs) are used as the main health outcome measure for the cost-utility analysis. Incremental cost effectiveness ratios (ICER) will be estimated using bootstrapping techniques and graphically presented on cost effectiveness planes. Sensitivity analysis on the most important assumptions will be performed in order to assess the robustness of the results.

QALYs will be calculated as the area under the health utility profile, with straight-line interpolation between utilities at each follow up. Utilities will be obtained using the EuroQol (EQ-5D) instrument. Health states will be estimated using reference values from a representative Dutch sample. ICER will be estimated using bootstrapping techniques and graphically presented on cost effectiveness planes. Sensitivity analysis on the most important assumptions will be performed in order to assess the robustness of the results.

The input of the implementation strategies will be assessed by collecting volumes of consumed resources and multiplying these by the price of each resource unit (market or guideline price). The output of the implementation strategies will be determined by the guidelines adoption rate, measured at fixed intervals during the study and the speed of adoption. Welfare losses will be determined by empirically established diffusion curves (one diffusion curve per strategy) and quantified by calculating the welfare change (monetarized variation in indicators/benchmarks compared to guideline) at the different time intervals adjusted for the complement of the adoption rate at a particular time interval. The decision criterion on which the efficient implementation strategy will be selected is the minimum welfare loss compared to the guideline programme over time (dynamic efficiency). The impact of variable(s) uncertainty on the decision criterion will be evaluated by sensitivity analyses.

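### The multilevel model names gynaecologist, patient and time as its levels but omits the hospital, the cluster on which the trial was sized

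*Protocol article*

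**What the plan says.** The protocol article describes the design under Study design: "A cluster randomised controlled trial with an economic evaluation alongside will be performed".

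Under Sample size, clustering is attached to the hospital: "Considering an intracluster correlation of 0.05, 20 hospitals will have to be included with approximately 20 patients each". The error rates are given as "alpha = 0.05; power = 0.80", for 34% against 17% major maternal complications, and the total follows from an allowance for loss: "If it is assumed that 15% of participants will drop out or be lost to follow up, 472 eligible women will have to be included".

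Under Data analysis, two effectiveness analyses are planned: "The analysis will include an elementary head-to-head comparison of the two intervention groups, as well as a multi-level analysis". The levels of the second are then listed: "The latter will incorporate the levels of gynaecologist, patient, and time measurements".

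The only other mention of the multilevel analysis, under Participants, adds patient characteristics as covariates. No section adds a hospital level.

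**The concern.** The sample size and the analysis name different clusters. Women in one hospital share its allocation. Gynaecologists in one hospital share it too, so they are not independent units in the comparison of strategies. A model with gynaecologist as its highest grouping counts colleagues in the same hospital as separate evidence.

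An article may leave modelling detail to a fuller plan. Here it does not stay silent: it lists the levels, and the list lacks the unit that its own sample size is built on. An analyst who follows the sentence literally would fit the wrong model. Standard errors would be too small, and the trial could claim that decision support is effective when it is not.

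**Working it through.** **Inputs.** From Sample size: 34% against 17%, alpha 0.05, power 0.80, ICC 0.05, 20 hospitals, about 20 women per hospital, 15% loss, total 472. Assumed: two-sided alpha and ten hospitals per arm. Not given: the number of gynaecologists per hospital.

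**1. Reproduce the plan's total.**
- Two proportions, pooled variance, no continuity correction: n per arm = [1.96 × √(2 × 0.255 × 0.745) + 0.8416 × √(0.34 × 0.66 + 0.17 × 0.83)]² / 0.17², which is just over 102 and rounds up to 103.
- Design effect with the hospital as cluster: 1 + (20 − 1) × 0.05 = 1.95.
- Total: 2 × 103 × 1.95 = 401.7, and 401.7 / 0.85 = 472.6, so 473. Starting from 20 × 20 = 400 gives 400 / 0.85 = 470.6, so 471. The stated 472 lies between them.
- Without the design effect, 206 / 0.85 = 242.4, so 243. The stated total therefore depends on hospital-level clustering.

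**2. Clustering ignored.**
- Type I error = 2 × [1 − Φ(1.96 / √1.95)] = 2 × [1 − Φ(1.404)] = 0.160.
- Interval width relative to the correct width: 1 / √1.95 = 0.72, or 28% too narrow.

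**3. Gynaecologist level only.** Assume that all clustering is at hospital level with ICC 0.05 and that the 20 women are split equally, g per gynaecologist. The model then allows for 1 + (g − 1) × 0.05, where the truth is 1.95. Type I error = 2 × [1 − Φ(1.96 / √(1.95 / modelled))].

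| Gynaecologists per hospital | g | Modelled design effect | Type I error, formula | Type I error, simulation |
|---|---|---|---|---|
| 1 | 20 | 1.95 | 5.0% | 6.5% |
| 2 | 10 | 1.45 | 9.1% | 10.0% |
| 4 | 5 | 1.20 | 12.4% | 13.0% |
| 5 | 4 | 1.15 | 13.2% | 13.5% |
| 10 | 2 | 1.05 | 15.0% | 15.3% |

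The simulation used 40,000 null trials per row (20 hospitals × 20 women, beta-binomial, event rate 0.34, ICC 0.05) and a normal reference. In the same runs the test that ignores clustering gave 16.0–16.2%.

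**4. Hospital level included.** The simulated error was 4.7–5.1% with a t reference on 18 degrees of freedom, and 6.2–6.6% with a normal reference. With 20 clusters the small-sample correction therefore matters.

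**5. Sensitivity to the ICC, clustering ignored.** ICC 0.01 gives 7.2%, 0.02 gives 9.5% and 0.10 gives 25.0%. The plan's own value is 0.05.

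**The case against.** The best defence is that the size of the error in the multilevel model is not known. It turns on the number of gynaecologists per hospital, which the article does not state; with one per hospital, the gynaecologist and hospital levels coincide and nothing is lost beyond the small-sample effect. This stands, so the result must be given as a range.

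The 16% belongs to an analysis that ignores clustering altogether. The article does not say that the head-to-head comparison is a confirmatory test, or on what unit it is run; it could be a descriptive table or a comparison of hospital rates. This also stands: the figure shows what happens if that comparison is used as a patient-level test.

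Measurements are planned before and after implementation. If the effect were tested as group-by-time, stable hospital effects would largely cancel, and the inflation would depend on hospital-by-period variation, which is not given. That is true, but no such test is stated, and the sample size is for a between-group difference.

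That hospitals are the randomised units is inferred from the sample size; the randomisation flowchart is not shown. The inference is strong, because the total cannot be reproduced without hospital-level clustering.

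Three stronger readings are tempting, and the article supports none of them.
- A reader might infer that the cost-effectiveness bootstrap also ignores clustering. The Economic evaluation section does not state the resampling unit, so there is nothing there to call wrong.
- A reader might infer that a time level is misplaced because the primary outcome occurs once per woman. The sentence also covers secondary outcomes and process indicators, women are followed for six months, and some data may be repeated within a woman.
- A reader might take 472 / 20 = 23.6 women per hospital, a design effect of 2.13, and an error of about 18%. That count is before the 15% loss; the analysis is sized on about 20 per hospital.

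**Conclusion.** The point holds as an internal contradiction: the trial is sized on hospitals as clusters, and the listed model levels leave the hospital out. That conclusion needs no assumption about gynaecologists and is not weakened by the article's brevity.

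The size is conditional. For a between-group test after implementation, at ICC 0.05 and 20 women per hospital, the two-sided type I error is about 16% if clustering is ignored, and between about 5% and 15% with a gynaecologist level only. A reader might infer that the planned effectiveness test would certainly run at 12–16%. The article does not support that: for the listed model, 12% or more requires about four or more gynaecologists per hospital, and the figure would change under a group-by-time test or a different ICC. The level should still be corrected before analysis, because the omission bears on the validity of the primary effectiveness comparison and costs little to repair.

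**What to change.** In the Data analysis section, name hospital as the top level: women, optionally within gynaecologists, nested in hospitals, with a random hospital effect and a small-sample correction for 20 clusters. A time level can stay for outcomes measured repeatedly. State that the head-to-head comparison is descriptive, or run it on hospital-level rates.

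The cost is wording and model code, with no new data. Intervals become wider, but correct. The sample size already includes the design effect of 1.95, so most of this widening has been allowed for. The small-sample correction takes a little more power, which the reproduced sample-size formula does not include because it uses normal quantiles.
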